# The effect of Mediterranean diet on nutritional status, muscle mass and strength, and inflammatory factors in patients with colorectal cancer-induced cachexia: study protocol for a randomized clinical trial

**DOI:** 10.1186/s13063-022-06985-4

**Published:** 2022-12-14

**Keywords:** Cancer cachexia, Colorectal cancer, Mediterranean diet, Nutritional status, Inflammation, Muscle health

## Abstract

**Background:**

Current dietary strategies to manage cancer cachexia and the relevant outcomes did not provide a comprehensive solution. This study will evaluate the effect of a Mediterranean diet on inflammatory markers, nutritional status, muscle mass, and strength among patients with cancer cachexia (CC).

**Methods:**

This will be a randomized clinical trial involving men and women diagnosed with localized or advanced colorectal cancer-induced cachexia. In total, 40 patients with CC will be recruited based on inclusion criteria and then these patients will be randomly allocated to receive either a Mediterranean diet (*n* = 20) or only routine nutritional advice (*n* = 20) for 8 weeks. The primary outcome will be nutritional status, muscle mass and strength, and serum concentrations of inflammatory markers including interleukin-6 (IL-6), tumor necrosis factor-alpha (TNF-α), and high-sensitive C-reactive protein (hs-CRP). Moreover, we will consider serum albumin and total protein levels, complete blood count (CBC), and quality of life as the secondary outcomes. All outcomes will be measured at the beginning and end (the eighth week) of the study. We will assess participants’ adherence to the prescribed diets by using a 1-day food record in the second, fourth, sixth, and eighth weeks of the study.

**Discussion:**

Along with adequate calorie and protein intake in cancer cachexia, reducing inflammatory cytokines might be a useful strategy for maintaining nutritional status and body composition. Mediterranean diet has been shown to have anti-inflammatory properties, and by its components, it might help patients with cachexia to have a better nutritional status and quality of life.

**Trial registration:**

Iranian Registry of Clinical Trials (www.irct.ir) RCT20211027052884N1. Prospectively registered on November 09, 2021.

**Supplementary Information:**

The online version contains supplementary material available at 10.1186/s13063-022-06985-4.

## Background

Cancer cachexia (CC), defined as a multifactorial syndrome associated with continuous loss of skeletal muscle mass (with or without fat loss), accounts for 50% of all deaths in patients with cancer [1, 2]. Despite the prevalence of this condition among most cancer patients, 50% of patients with colorectal cancer are at risk to develop cachexia [3]. It is associated with reduced quality of life, increased length of hospital stays, increased healthcare costs, and elevated risk of mortality [1].

Systemic and acute inflammation plays a major role in the pathophysiology of CC [4]. Increased concentrations of inflammatory factors in these patients disrupt the function of leptin, ghrelin, neuropeptide Y, and the neuroendocrine axis, thereby continuously stimulating the anorexia pathways [4] and inducing hypercatabolic states, muscle destruction, and increased lipolysis [4]. On the other hand, chemotherapy and radiotherapy in these patients further exacerbate these conditions through increasing nausea, dysphagia, mucositis, and malabsorption [4]. Earlier studies have examined the effect of nutritional counseling on these patients and reached conflicting findings. While some investigators reported the efficacy of nutritional counseling on increasing energy and protein intakes in patients with CC, such diets did not result in significant changes in body weight, muscle mass, and strength [5, 6]. Mediterranean diet has been shown to effectively reduce inflammation [7, 8], cancer incidence, and mortality [9]. On the other hand, a significant positive relationship was seen between adherence to the Mediterranean diet and muscle mass and strength [10]. Consumption of the Mediterranean diet was also protectively associated with frailty and functional disability, as indicators of skeletal muscle function [11]. Despite the protective associations between the consumption of the Mediterranean diet and cancer and muscle health, we are aware of no clinical trial examining the effect of the Mediterranean diet on cancer cachexia. This dietary pattern is due to a high content of monounsaturated fatty acids (MUFA), polyunsaturated fatty acids (PUFA), oleuropein, hydroxytyrosol, polyphenols, B vitamins, antioxidant vitamins, and minerals which present in plant foods, fish, nuts, and extra virgin olive oil, which has been associated with anti-inflammatory properties through reducing arachidonic acid, inflammatory prostaglandins, and leukotrienes [12, 13]. Reducing inflammation through upregulating insulin and insulin-like growth factor-1 (IGF-1) which decrease protein degradation can elevate overall muscle health [14]. The current clinical trial will therefore be done to examine the effectiveness and superiority of the Mediterranean diet on nutritional status, muscle mass and strength, and inflammatory factors in patients with cancer-induced cachexia compared to routine nutritional care.

## Methods

### Participants

This will be a randomized effectiveness controlled clinical trial among patients with localized or advanced colorectal cancers whose type of cancer will be confirmed by an oncologist through histopathology. Patients will be selected based on inclusion criteria from Imam Khomeini hospital, Tehran University of Medical Sciences in Tehran, Iran. Furthermore, the trial has been registered at www.irct.ir (IRCT20211027052884N1) on November 09, 2021. All items from the World Health Organization Trial Registration Data Set can be found within the current protocol that is registered in the Iranian Clinical Trials registry. The flow diagram of the study design is shown in Fig. 1.

**Fig. 1 Fig1:**
[figure not shown]
Flowchart of the study

### Inclusion criteria

In the study, we will recruit patients who have the following criteria: (1) patients with colorectal cancers in stages II–IV according to the TNM UICC 2010 method (based on the oncologist diagnosis) [15]; (2) patients with cachexia according to the Global Leadership Initiative on Malnutrition (GLIM) criteria [16]; (3) successful qualification to first-line radiotherapy or chemotherapy according to guideline [17]; (4) patients’ functional status is at least ≥70% according to Karnofsky scale [18]. The lower Karnofsky score indicates the lower chances of surviving; (5) individuals who have no contraindications for oral feeding and are able to be fed orally; (6) patients without acute uncontrolled underlying diseases such as kidney and/or liver failure; (7) patients at age 40 or older; and (8) men or women.

### Non-inclusion criteria

Patients with the following conditions will not be included in the study: (1) patients who need nutritional support (tube or intravenous feeding) and (2) patients with a history of allergy to any component of the Mediterranean diet, such as olive oil or nuts.

### Exclusion criteria

Patients who meet the following conditions will be excluded from the study and will not be included in the per-protocol analysis: (1) patients who die during the study; (2) patients with less than 60% adherence to the Mediterranean diet based on the prescribed energy and macronutrients; (3) individuals who change their eating route from oral feeding to enteral or parenteral feeding throughout the study; (4) patients that are not willing to continue the study for any reason; and (5) patients who change their treatment protocol during the study.

### Study design

After obtaining informed written consent, all required measurements will be performed at the beginning of the study. Then, stratified block randomization will be done based on the type of cancer (colon or rectum) and BMI (≤23, > 23) using the www.randomization.com website. The statistician will fold the paper containing a randomization number and put them in the envelopes and write the code on them. The envelopes will be kept at the enrollment center. Then, for each qualified patient, the nutritionist randomly picks one of the envelopes after shuffling and allocates patients into control and intervention groups. It is not possible to blind study participants or staff in this study due to nutritional interventions. Nevertheless, the outcome assessor will be blinded to the group assignment.

Regarding colorectal cancer treatment, subjects with rectal cancer undergoing first-line radiotherapy and subjects with colon cancer undergoing first-line chemotherapy with capecitabine and oxaliplatin (CAPOX), 5-fluorouracil-leucovorin-irinotecan (FOLFIRI), 5-fluorouracil and oxaliplatin (FOLFOX), or capecitabine will be included [17]. As explained, people will be placed in separate blocks based on the type of cancer. The duration of the study for both intervention and control groups will be 8 weeks. Participants in the intervention group will receive a Mediterranean diet menu along with extra virgin olive oil, while participants in the control group will receive nutritional advice for cancer patients and dietary recommendations for weight gain. To assess participants’ adherence to the proposed diets, a 1-day food record will be used in the second, fourth, sixth, and eighth weeks of the study. Moreover, to encourage patients to follow the diet, all patients will be contacted weekly during the study. Participants will be asked to maintain their normal daily activities during the study. In addition, individuals’ physical activity will be monitored through completing a 1-day record in the second, fourth, sixth, and eighth weeks of the study. At the end of the study, all required measurements will be taken again in both groups. A Standard Protocol Items: Recommendations for Interventional Trials (SPIRIT) diagram for the trial schedule is indicated in Fig. 2.

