### Limitations

The most distinctive biomarker for examining adherence to the Mediterranean diet is the assessment of serum and urine hydroxytyrosol levels [34]. However, we will be unable to assess this biomarker as a measure of patients’ adherence to the Mediterranean diet due to limited funding. Therefore, we will use the average of four 24-h dietary records throughout the study to examine adherence to the prescribed diets. Although different modalities of cancer treatment may have an influence on nutritional status, we will stratify patients based on the type of treatment they receive. Moreover, it should be mentioned that blinding is impossible, and the risk of bias might be possible.

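### Envelopes drawn from stratified block randomization are shuffled and picked for each patient, so the block order is not used and balance within strata is not guaranteed

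*Protocol article*

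**What the plan says.** All of the allocation procedure stands in the Study design section of the protocol article.

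- **Method.** After consent and baseline measurements, "stratified block randomization will be done based on the type of cancer (colon or rectum) and BMI", with two BMI classes cut at 23 and a list produced by a randomization website. Two cancer sites and two BMI classes make four strata.
- **Preparation.** "The statistician will fold the paper containing a randomization number and put them in the envelopes and write the code on them".
- **Storage.** "The envelopes will be kept at the enrollment center".
- **Allocation.** For every patient who qualifies, "the nutritionist randomly picks one of the envelopes after shuffling and allocates patients into control and intervention groups".
- **Blinding.** The section says that neither participants nor staff can be blinded; only the outcome assessor is.
- **Separation by site.** The next paragraph has rectal patients on radiotherapy and colon patients on chemotherapy, and adds that patients go into separate blocks by cancer type.

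The Limitations section concedes that treatment modality may influence nutritional status and answers that "we will stratify patients based on the type of treatment they receive". Because site determines modality here, this refers in effect to the site stratification.

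**The concern.** A stratified permuted-block list works through its order. Within a stratum, every completed block holds equal numbers of each arm, so the running difference between arms can never be large. Shuffling the envelopes before each pick removes the order and replaces the list with a draw from an urn. The section therefore describes two different mechanisms, and the one that would be carried out is not the one named.

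Two things are at stake. The first is balance. The Limitations section offers stratification as its answer to differences in cancer treatment, and the Statistical analysis section names only the baseline value of the outcome as a covariate, not cancer site or BMI. If the allocation does not deliver the balance, no stated analysis step compensates for it.

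The second is control of the draw. With no fixed order there is no next envelope. If someone who cannot be blinded were to discard a draw and pick again, the sequence of assignments could not be compared with the list to show it.

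**Working it through.** The article gives no figure for expected imbalance, so there is none to reproduce.

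**Inputs from the article.** 40 patients, 20 per arm (Abstract, Methods; Sample size calculation). Four strata (Study design).

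**Assumptions.** Stratum sizes, block sizes and pack sizes are not given. I take four strata of 10, equal numbers of each arm in every pack, and draws without replacement. A bad split means 7:3 or worse in a stratum of 10, an arm difference of at least 4.

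**Formula.** From a pack of M envelopes, half for each arm, the number X assigned to the Mediterranean diet among 10 draws is hypergeometric: P(X = x) = C(M/2, x) · C(M/2, 10 − x) / C(M, 10). A bad split is X ≤ 3 or X ≥ 7.

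1. **Blocks of 4, used in order.** Ten patients are two full blocks (4:4) plus two patients from a third. The worst case is 6:4, so P = 0.

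2. **One mixed pack of 40.** For a given stratum, P = 0.273. For at least one of four, count the allocations in which every stratum lies between 4 and 6: 49,307,934,816 of C(40, 20) = 137,846,528,820. So P = 1 − 0.358 = 0.642.

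3. **Separate stratum packs of 20 envelopes.** C(20, 10) = 184,756. The number of ways with X ≤ 3 is 1 + 100 + 2,025 + 14,400 = 16,526. Doubling gives 33,052 / 184,756 = 0.179 per stratum. For at least one of four, 1 − (1 − 0.179)⁴ = 0.545.

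4. **One pack of 20 per cancer site, all used.** Each site ends exactly 10:10. The two BMI strata within a site mirror each other (7:3 in one forces 3:7 in the other), so P = 0.179 per site. For at least one of two sites, 1 − (1 − 0.179)² = 0.326.

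5. **Stratum packs of 12 envelopes.** Only six envelopes exist per arm, so 10 draws cannot be worse than 6:4: P = 0. With 14 envelopes, P = 0.070 per stratum and 1 − (1 − 0.070)⁴ = 0.252 for at least one of four.

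| How the envelopes are pooled | At least one stratum 7:3 or worse |
|---|---|
| Blocks of 4 in list order | 0 |
| Shuffled, 12 per stratum | 0 |
| Shuffled, 14 per stratum | 25% |
| Shuffled, one pack of 20 per site | 33% |
| Shuffled, 20 per stratum | 55% |
| Shuffled, one pack of 40 | 64% |

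**Unequal strata.** A simulation of 20,000 runs with strata of 14, 12, 8 and 6 gives an arm difference of 4 or more in at least one stratum with probability 0.62 (one pack of 40), 0.50 (stratum packs of 20) and 0 (blocks of 4 in order). The picture does not depend on equal strata.

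**The case against.** The strongest case against has four parts.

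**The worst figure needs a reading that the text points away from.** The 64% requires one pack with all strata mixed, while Study design also says that patients are placed in separate blocks by cancer type. With one pack of 20 per site, site and hence treatment modality balance exactly, and only BMI within site is exposed. With small stratum packs nothing is lost. This stands: a reader might infer that balance on cancer site is forfeited, but the article does not establish that.

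**An honest draw is still randomization.** Shuffling causes no bias. Chance imbalance costs some precision, and even with one pack of 40 a split of 14:6 or worse within a site of 20 has a probability of only 2.6%. The baseline value of the outcome is adjusted for, and the outcome assessor is blinded. This also stands and limits the harm. Blinded assessment does not, however, remedy selection at the moment of allocation.

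**Concealment is not shown to be lost.** A reader might infer that allocation is unconcealed and beyond audit. The documents do not support that. The statistician prepares the envelopes and marks each with a code, consent and baseline measurements come first, and sealing, opacity and logging are details that a condensed article may omit. The text says that the pick is random; influence is an opportunity, not a described practice. What remains is narrower: the article prescribes a step that removes the fixed order against which assignments could be checked.

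**Shuffling makes the next assignment harder to guess** than fixed blocks in an open trial. This is true, and the fix has to deal with it.

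None of these reconciles the two statements. Only shuffling inside a single block would preserve block balance in general, and nothing in the text says that this is what is done.

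**Conclusion.** The point holds as an internal contradiction. The article names stratified block randomization and then prescribes a per-patient shuffle that does not use the block order, so balance within strata is not guaranteed. This is an affirmative instruction, not a detail left out of a condensed article.

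Assuming four strata of 10 and draws without replacement, the chance that at least one stratum splits 7:3 or worse lies between 0 and about 64%, depending on how the envelopes are pooled, against 0 for blocks of 4 in order. No single value in that range can be claimed, because pack, block and stratum sizes are not stated. The comparison of arms stays unbiased if the draws are honest. The second harm, an opportunity for unblinded staff to select or repeat a draw, cannot be quantified and is not alleged to have occurred. The sample size is unaffected.

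It should be corrected now: the Trial status section says that enrolment is under way, and allocation cannot be repaired after the last patient is randomized.

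**What to change.** Delete the shuffle-and-pick step. For the remaining patients, use sequentially numbered envelopes, one series per stratum in list order. Write the patient's ID and the date on the next envelope before opening it. Preferably have the statistician or someone outside recruitment hold the envelopes, if this needs no extra staff. Record which patients were already allocated by shuffling, how the envelopes were pooled at the time, and report both with the results.

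Ordered blocks are somewhat more predictable than a shuffled pack in an unblinded trial, so vary the block sizes and withhold them from the nutritionist.

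The cost is one paragraph of protocol text and rebuilding the remaining series mid-trial, since the current packs have been depleted by random draws. That is more than relabelling, but small for a trial of 40.

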**Fig. 2 Fig2:**
[figure not shown]
SPIRIT diagram of the recommended content for the schedule of enrolment, interventions, and assessments

### Intervention

The main intervention in this study is the administration of a Mediterranean diet. The energy required by patients in the intervention group will be computed according to the recommendations of the ASPEN guideline [19]. First, we will start with 25 kcal per kg of the current body weight and then gradually will move over 2 weeks to 35 kcal. Energy will be divided as follows between the macronutrients [20]: 35% of calories from fat (less than 7% saturated, 10–15% PUFA and the rest from MUFA), 45% of calories from carbohydrates, and 20% of calories from proteins. Then, by emphasizing the recommended food groups in the Mediterranean diet, the supply of these macronutrients from different food groups will be considered. Based on these food groups, a weekly dietary menu will be written for each patient. The Mediterranean diet will be designed based on the following recommendations: the use of extra virgin olive oil for cooking salads and other foods (participants will be given “extra virgin olive oil” free of charge), consumption of two or more exchanges per day of vegetables, three or more exchanges per day of fresh fruit, three or more exchanges per week of legumes, two or more exchanges per week of fish or seafoods, and three or more exchanges per week of nuts or seeds will be highlighted. The use of white meats instead of red or processed meats will also be focused. There will be also some recommendations to limit the consumption of butter, cream, fast foods, sweets, and sugary drinks. To increase the adherence to the dietary intervention, all the dietary menus will be personalized based on dietary habits of each person in the study.

In the control group, routine nutritional recommendations about weight gain and prevention of weight loss in cancer patients based on the clinical guidelines [21] will be given as brochures. All the points in these brochures will be explained to patients orally in a training session. As mentioned above, this group of patients, like the patients in the intervention group, will be followed up during the study period.

### Assessment of study outcomes

In the current study, the main primary outcome would be nutritional status, fat-free mass, muscle strength, and inflammatory markers including interleukin-6 (IL-6), tumor necrosis factor-alpha (TNF-α), and high-sensitive C-reactive protein (hs-CRP). Moreover, the following variables will be considered as the secondary outcome: serum albumin and total protein, complete blood count (CBC), and quality of life. All primary and secondary outcomes will be assessed at the beginning and end (the eighth week) of the study.

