### Sample size calculation

The sample size required for the current study was calculated using the formula (*n* = 2 [(*z*1−*α*/2 + z1−*β*)^2^ · *s*^2^]/*d*^2^), which has been proposed for parallel clinical trials [24]. Considering the nutritional status (score obtained from the PG-SGA questionnaire) as the key variable [25], type I error of 5% (*α* = 0.05), type II error of 20% (*β* = 0.20, study power = 80%), standard deviation of PG-SGA score (*S*= 4.1), and *d* as equal to 3.9 [25], the required sample size for each group will be 17 patients. However, to ensure a sufficient sample size at the end of the study and taking into account the 15% probable dropout, 20 patients in each group will be recruited according to the inclusion criteria. Considering that the samples will be given in this project are among the patients referred to the radio-oncology clinic and introduced by the radio-oncology specialist, therefore, while ensuring the correct selection of samples based on the inclusion criteria, the number of patients is sufficient to reach the desired sample size for this research project.

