### Statistical analysis

Statistical analysis will be performed according to the intention-to-treat protocol; however, a per-protocol analysis will also be done. Thus, all randomized patients who have followed the Mediterranean diet for at least 2 weeks and who have the baseline measurements will be analyzed. With regard to missing data, the mean of each variable will be used to replace missing data. First, we will apply the Kolmogorov-Smirnov test to determine the normality of variables. In case of the non-normal distribution of a variable, a logarithmic transformation will be conducted. Independent sample’s *t*-test (or its non-parametric test Mann-Whitney *U*) will be used to compare the baseline values ​​of continuous variables between the two groups. Moreover, the chi-square test will be conducted to compare categorical variables. To examine the effect of the Mediterranean diet on the outcome variables, we will apply repeated measures ANOVA, in which the effect of time, intervention, and time*intervention interaction will be explored. In addition to the investigation of the crude means of variables in this analysis, we will compute adjusted means of outcome variables taking into account the baseline levels of the relevant variables. Changes in outcome variables will also be examined between the two groups using an analysis of covariance, in which the baseline values will be considered as covariates. Data will be analyzed using SPSS software version 26. *P*-value <0.05 will be considered as statistically significant.

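### Six variables share the primary outcome at an unadjusted 0.05 with no rule for success, while the sample size rests on the PG-SGA score alone

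*Protocol article*

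**What the plan says.** Three parts of the protocol article bear on this.

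- **Outcomes.** Under Assessment of study outcomes, "the main primary outcome would be nutritional status, fat-free mass, muscle strength, and inflammatory markers including interleukin-6 (IL-6". The sentence continues with "tumor necrosis factor-alpha (TNF-α), and high-sensitive C-reactive protein (hs-CRP). Moreover, the following variables will be considered as the secondary outcome". Six variables are therefore primary: the PG-SGA score (the measure of nutritional status), fat-free mass, handgrip strength (the measure of muscle strength), IL-6, TNF-α and hs-CRP. The abstract does the same: "The primary outcome will be nutritional status, muscle mass and strength, and serum concentrations of inflammatory markers". It says muscle mass where the main text says fat-free mass.
- **Sample size.** The Sample size calculation section uses one variable: "Considering the nutritional status (score obtained from the PG-SGA questionnaire) as the key variable". It takes a two-sided 5% alpha, 80% power, SD 4.1 and difference 3.9. This gives 17 per group, raised to 20 for 15% dropout.
- **Analysis.** The Statistical analysis section treats all outcomes alike: "To examine the effect of the Mediterranean diet on the outcome variables, we will apply repeated measures ANOVA", followed by an analysis of covariance on changes. One threshold covers every test: a P-value "<0.05 will be considered as statistically significant". No order of testing, division of alpha or definition of a positive trial is given.

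**The concern.** The Background states a superiority aim, so a reader will expect to learn which result decides it. The outcomes section offers six equal candidates, whereas the sample size section treats one as leading. With a flat 0.05 and no success rule, the report could present whichever of the six crosses the threshold as the primary result, for instance a single cytokine when the PG-SGA score shows nothing. The error rate of the overall conclusion would then depend on a choice that the plan leaves open.

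This is more than detail left to a statistical analysis plan. The protocol itself fixes six primaries and an unadjusted threshold, and its own sections disagree on whether one variable leads. An adjustment added later in an analysis plan would also change the alpha on which the 17 per group was computed.

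**Working it through.** **Inputs.** From the Sample size calculation section: difference d = 3.9, SD s = 4.1, two-sided alpha 0.05, power 80%, dropout 15%. From Assessment of study outcomes: six primaries. From Statistical analysis: threshold 0.05 for each. Correlations among the six outcomes are not given, so a range is assumed.

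**1. The plan's own figure.** n = 2(1.960 + 0.842)² × 4.1² / 3.9² = 2 × 7.849 × 16.81 / 15.21 = 17.35 per group. The plan prints 17 (strict rounding up gives 18), and 17 / 0.85 = 20. The figure is reproduced, for the PG-SGA score only. The section gives no SD or difference for the other five variables.

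**2. If any one of six counts as success.** This takes one two-sided 0.05 test per outcome.

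- Independent outcomes: 1 − 0.95⁶ = 1 − 0.7351 = 0.265.
- Common correlation r between normal test statistics: 1 − ∫ φ(u) [Φ((1.96 − √r·u)/√(1−r)) − Φ((−1.96 − √r·u)/√(1−r))]⁶ du.

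| Assumed r | Chance of at least one false positive |
|---|---|
| 0 | 26.5% |
| 0.3 | 24.1% |
| 0.5 | 20.7% |
| 0.7 | 16.4% |
| 0.9 | 10.8% |

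A less uniform pattern, with the three inflammatory markers correlated at 0.5 to 0.7 and all other pairs at 0.1 to 0.3, gives about 22% to 25% by simulation. None of these figures counts the second planned analysis of each outcome.

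**3. If all six must be significant.** The chance of a false claim is then at most 5%, so there is no inflation. The difficulty moves to power, which cannot exceed that of the weakest outcome. As an illustration only, six independent outcomes with 80% power each would give 0.8⁶ = 26%; positive correlation would raise this. The document gives nothing from which to compute the actual value.

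**4. If alpha is split equally.** 0.05 / 6 = 0.0083. Power for the PG-SGA score comes from the noncentral t distribution with 2n − 2 degrees of freedom and noncentrality (3.9/4.1)√(n/2), which is 2.77 at n = 17 and 3.01 at n = 20.

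| n per group | Power at 0.05 | Power at 0.0083 |
|---|---|---|
| 17 | 76.7% | 49.4% |
| 20 | 83.4% | 59.2% |

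The first column is 77% rather than 80% at n = 17 because the plan's formula uses normal quantiles and 17.35 was rounded down. Each row uses one method throughout, so the drop is like for like. With alpha 0.0083, the plan's formula would need 27 per group, or 27 / 0.85 = 31.8, so 32 with dropout.

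**The case against.** The strongest reply is that the article never says one significant result out of six makes the trial positive. A reader might infer from the flat 0.05 that the trial carries a 21% to 26% chance of a false positive conclusion. The document does not support that as an unconditional statement: it contains no any-of-six rule and no correlations. The PG-SGA instrument also scores weight change, muscle loss and physical function, so it overlaps with fat-free mass and strength, and correlations above 0.5 cannot be excluded. This stands, and the figures must be read as conditional. What remains is that the plan does not exclude the any-of-six reading, and even at a correlation of 0.9 the rate is about twice 5%.

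A reader might also infer that the 5% in the sample size section is false. It is not. That figure is stated for the PG-SGA comparison alone, and testing other variables does not change it. The section makes no claim about the family of six.

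Third, the sample size section calls the PG-SGA score the key variable, and both outcome lists put nutritional status first. This suggests an intended lead outcome and makes the remedy a clarification rather than a redesign. It does not settle the matter, because the phrase serves only the sample size and the two outcome statements give all six the same rank.

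Finally, an analysis plan that is not shown might add an adjustment. That would help with error control, but an equal split would leave the PG-SGA test underpowered at the planned size, and the outcomes section would still disagree with the sample size section.

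**Conclusion.** The point holds in conditional form. The protocol names six equal primaries, tests each at an unadjusted 0.05, states no success rule, and is sized for one of them.

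- **Any one suffices:** the chance of at least one false positive is 26.5% under independence, falling to 11% at an assumed common correlation of 0.9, with one test per outcome.
- **All six required:** type I error is controlled, but power for that goal was never computed.
- **Equal split of alpha:** PG-SGA power drops to 49% at 17 per group, or 59% at the 20 recruited, against 77% and 83% at 0.05.

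The 49% and 59% describe that possible repair, not the plan as written. Of the readings considered, only a single PG-SGA primary at 0.05 matches the sample size section.

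**What to change.** Name the PG-SGA score at week 8, tested at two-sided 0.05, as the single primary outcome in the abstract and in Assessment of study outcomes. This agrees with the Sample size calculation section and leaves the planned 20 per group unchanged. List fat-free mass, handgrip strength, IL-6, TNF-α and hs-CRP as secondary outcomes that carry no confirmatory claim. Whether they are adjusted or reported as estimates with intervals can be left to the analysis plan.

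The Trial status section reports enrolment since January 2022, so the change should be a dated amendment with a written rationale, made before any between-group outcome comparison. The registry entry was not available for this review; it should be brought into line where needed.

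The cost is an amendment and the loss of primary status for five outcomes. No patients, visits or measurements are added.
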